One potentially promising and standardized approach is the National Acupuncture Detoxification Association (NADA) protocol, a specific form of auricular acupuncture originally developed as an adjunctive treatment in addiction medicine. The protocol consists of stimulation of 5 defined auricular points (sympathetic, shen men, kidney, liver, and lung) and is intended to promote emotional stabilization and support autonomic regulation [16,17]. Since its introduction, its application has expanded to other health care contexts, including the management of sleep disturbances [18,19], pain [20], or stress management [21,22]. Of particular relevance to perioperative medicine is its presumed stress-regulating effect. It is hypothesized that the NADA protocol modulates the autonomic nervous system, particularly by reducing sympathetic overactivity and enhancing parasympathetic tone, thereby attenuating anxiety and stress-related physiological responses [23]. Despite encouraging findings in other clinical contexts, the NADA protocol has been insufficiently investigated in oncology, particularly in the perioperative setting. Preliminary studies and case reports suggest potential benefits for patients with cancer, including those with breast and prostate cancer, especially in the management of endocrine therapy-related side effects, sleep disturbances, fatigue, anxiety, and depressive symptoms, while showing a low risk of adverse events [24-26]. However, systematic investigations in oncological settings remain limited, and rigorously designed randomized controlled trials are required to more clearly establish its efficacy, particularly with regard to its stress-regulating effects.

The present study aims to evaluate the effects of NADA auricular acupressure on perioperative anxiety and pain in patients with a first diagnosis of breast cancer undergoing therapeutic breast surgery. In addition, we will exploratorily assess whether this intervention further impacts decisions regarding the initiation or use of other complementary and integrative medicine (CIM) therapies within the first 3 months following surgery.

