### Sample Size Calculation

As this is, to the best of our knowledge, the first study investigating the effects of ear acupressure on preoperative anxiety, we opted for a clinically meaningful effect to be the most appropriate basis for the sample size calculation [31,32]. The sample size was determined to ensure adequate statistical power to detect a clinically important difference between groups on the (STAI-S) [33]. Based on an 8-point minimal clinically important difference [34] and assuming an SD of 10 based on previous data in similar populations [35], this amounts to a large effect size (Cohen *d*=0.8; *f*=0.4).

The sample size estimation was performed using G*Power (version 3.1, Heinrich Heine University Düsseldorf, Germany) [36] specifying a covariance analysis (ANCOVA) with the treatment group as the between-subject factor and the baseline STAI-S score as a covariate, a 2-sided significance level of 5%, and a statistical power of 80%. This yielded a required total sample size of 52 patients. To account for an anticipated dropout rate of 20%, a total of 66 participants will be enrolled in the study.

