#### Control Group: Standard Care (CTRL)

Participants allocated to the control group will receive standard preoperative care according to institutional practice. No auricular acupressure will be administered prior to surgery. To promote fairness between study groups, participants in the control group will be offered NADA auricular acupressure after completion of the last study measurement on the day of hospital discharge.

No restrictions will be placed on standard hospital procedures in either study group during the study period.

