### Outcomes

Data will be collected at the following time points: baseline (T0), prior to surgery (T1), after transfer to the surgical ward following surgery (T2), daily during the postoperative hospital stay until discharge or up to a maximum of 10 days, whichever occurs first (T3-Tx), and at 3-month follow-up (T_FU_). An overview schedule of enrollment, interventions, and assessments is presented in Figure 1 [28].

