All analyses will be conducted according to the intention-to-treat (ITT) principle. All randomized participants will be included in the analysis and analyzed according to their allocated group, irrespective of adherence to the intervention. Missing data will be handled using multiple imputation by chained equations (MICE) under the assumption that data are missing at random using the “mice” package for R [46]. Due to the nature of longitudinal data collection, between-participant variation in number of hospitalization days is expected and will be accounted for. Observations expected during hospitalization but not available will be imputed; however, measurements not collected because of hospital discharge will not be imputed. Analyses will be performed on multiply imputed datasets, and parameter estimates across the imputed datasets will be combined using Rubin’s rule.

As a sensitivity analysis, a per-protocol analysis will be conducted, including only participants who adhered to their allocated treatment. Protocol adherence will be defined a priori. Participants in the intervention group will be considered protocol-adherent if they received the ear acupressure prior to surgery and continued the intervention for the subsequent 4 days or until hospital discharge, whichever occurred first. Participants in the control group will be considered adherent if they did not receive ear acupressure before the end of primary data collection (Tx).

In addition, an exploratory exposure-based sensitivity analysis will be performed at 3 months follow-up to assess the association between exposure to ear acupressure and the use of other CIM therapies. To this end, participants will be classified according to actual exposure to ear acupressure, defined as receipt of ear acupressure either during the intervention phase or after discharge in the control group. ORs and corresponding 95% CIs will be calculated to compare the likelihood of using CIM therapies between participants exposed to ear acupressure and those not exposed.

No formal adjustment for multiplicity will be applied, as the trial has a single primary outcome for the confirmatory analysis. Findings for the secondary outcomes, as well as the moderation and sensitivity analyses, are considered subsidiary and exploratory [47].

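### The only analysis spelled out for 3-month CIM use compares patients by actual acupressure exposure, which controls choose at discharge; its odds ratio is biased upward if that choice tracks interest in CIM

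*Protocol article*

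**What the plan says.** The aim is put in causal terms. The Introduction, like the Abstract, says "we will exploratorily assess whether this intervention further impacts decisions regarding the initiation or use of other complementary and integrative medicine (CIM) therapies" in the first 3 months after surgery. The Outcomes section lists therapy decisions at follow-up among the secondary outcomes, to be collected by a self-developed questionnaire.

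Controls may receive the intervention before that outcome is measured. Under Control Group: Standard Care (CTRL), they "will be offered NADA auricular acupressure after completion of the last study measurement on the day of hospital discharge". The assessment schedule in Outcomes runs beyond the hospital stay "and at 3-month follow-up".

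The analysis of this outcome is described once, near the end of Data Analysis: "participants will be classified according to actual exposure to ear acupressure, defined as receipt of ear acupressure either during the intervention phase" or, in the control group, after discharge. Odds ratios with 95% CIs then compare exposed with unexposed participants. No covariates are named. The text calls this an exploratory, exposure-based sensitivity analysis of an association.

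Earlier in Data Analysis, every analysis is said to follow intention to treat, with participants kept in their allocated group. A logistic model is named for postoperative complications; none is named for CIM use.

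**The concern.** Exposure is settled by randomisation in one arm and by personal choice in the other. A control who accepts the discharge offer joins the exposed group; one who declines stays unexposed. Apart from any NADA patient who was never treated, the unexposed group is therefore the controls who declined a complementary therapy, and the outcome is the use of other complementary therapies. If the two decisions share a cause, such as general interest in CIM, the decliners will show lower use whether or not acupressure has any influence.

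None of the named baseline scales (APAIS, STAI-T, BDI-II) measures interest in CIM, so they offer no direct adjustment for it. The analysis is called a sensitivity analysis, but the article describes no by-arm CIM analysis for it to be set against. At stake is how the 3-month result is read: an odds ratio above 1 could be taken as the intervention prompting further CIM use when selection alone could produce it.

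**Working it through.** **The plan's own figure.** No figure is given for the CIM analysis. The stated sample size fixes the group sizes and reproduces. With f = 0.4, two groups, one covariate, two-sided 5%, noncentrality f²N and N − 3 denominator degrees of freedom, ANCOVA power is 0.799 at N = 51 and 0.807 at N = 52, in line with "This yielded a required total sample size of 52 patients". Allowing 20% dropout, 52 / 0.8 = 65, and 66 is the next even number. At 1:1 that is 33 per arm.

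**Assumptions.** The protocol gives no CIM-use rate and no uptake rate among controls, so these are assumed and varied. Half of patients are CIM-inclined. Later CIM use is h in the inclined and l in the others. Controls accept the offer with probability u1 (inclined) or u0 (others). Acupressure has no effect on CIM use, all 33 NADA patients are treated, and all 66 are followed up.

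**Formulas.**
- Overall use: p = 0.5h + 0.5l
- Control uptake: a = 0.5·u1 + 0.5·u0
- Use in accepting controls: p_acc = (0.5·u1·h + 0.5·u0·l) / a
- Use in declining controls: p_dec = [0.5(1 − u1)h + 0.5(1 − u0)l] / (1 − a)
- Use in the exposed: p_exp = (p + a·p_acc) / (1 + a)
- Null odds ratio = odds(p_exp) / odds(p_dec)

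Because p = a·p_acc + (1 − a)·p_dec, the difference p_exp − p_dec equals 2a(p_acc − p_dec) / (1 + a). With no effect it is positive exactly when accepting controls use more CIM than declining controls, and zero when they do not differ.

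**One case in full** (h = 0.7, l = 0.3, u1 = 0.9, u0 = 0.5):
- p = 0.5; a = 0.7
- p_acc = (0.315 + 0.075) / 0.7 = 0.557
- p_dec = (0.035 + 0.075) / 0.3 = 0.367
- p_exp = (0.5 + 0.39) / 1.7 = 0.524
- Exposed: 33 × 1.7 = 56.1. Unexposed: 33 × 0.3 = 9.9
- Null odds ratio = (0.524/0.476) / (0.367/0.633) = 1.90

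**Range.** Rejection is the share of 20,000 simulated null trials in which a two-sided 5% Wald test (0.5 added to each cell) rejects.

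| Later use h / l | Acceptance u1 / u0 | Expected unexposed | Null OR by exposure | Rejection |
|---|---|---|---|---|
| 70% / 30% | 60% / 60% | 13.2 | 1.00 | 3.3% |
| 70% / 30% | 30% / 10% | 26.4 | 1.18 | not run |
| 60% / 40% | 70% / 30% | 16.5 | 1.24 | 5.3% |
| 70% / 30% | 50% / 10% | 23.1 | 1.42 | not run |
| 70% / 30% | 70% / 30% | 16.5 | 1.54 | 9.0% |
| 70% / 30% | 80% / 40% | 13.2 | 1.66 | 9.5% |
| 70% / 30% | 90% / 50% | 9.9 | 1.90 | 8.7% |
| 80% / 20% | 90% / 50% | 9.9 | 2.69 | 18.2% |

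**By randomised arm.** Both arms have expected use p under no effect, so the odds ratio is 1.00 in every row. The same test rejects in 3.6% to 3.8% of trials in the six simulated scenarios.

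The unexposed group shrinks as uptake rises. If every control accepted and every NADA patient was treated, it would be empty and the odds ratio could not be estimated.

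**The case against.** The case on the other side has several parts, and most of it limits the point without removing it.

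- **It is not a contrast of volunteers with decliners.** A reader might infer that it is. The exposed group is the treated NADA patients plus accepting controls; in the case worked above, 33 of about 56 are there by randomisation. This dilutes the selection. A pure acceptor-versus-decliner odds ratio would be 1.91 rather than 1.54 in the 70/30 use, 70/30 acceptance case, and 3.30 rather than 2.69 in the last row. This stands.
- **The bias is conditional.** It needs acceptance to track interest in CIM. All participants agreed to join an acupressure trial and were recruited through a Department of Integrative Medicine, which may narrow the spread of interest. With no link the odds ratio is 1.00, and at low uptake it is modest (1.18). This also stands.
- **Intention to treat is declared for all analyses.** The Abstract mentions logistic regression as appropriate, and the exposure analysis is introduced as an addition. A reader might infer from its being the only one described that no by-arm CIM analysis is intended. The article does not show that, and a full analysis plan may contain one. What remains is that the one analysis the article does spell out departs from its own intention-to-treat statement and does not fit the stated aim.
- **The label is modest.** The text says exploratory and association, and treats sensitivity analyses as subsidiary. It makes no causal claim for this odds ratio. That lowers the stakes, but the objective it sits under asks about impact.
- **The discharge wording.** A reader might see a contradiction between a last measurement at discharge and a later follow-up. The control-group text plausibly means the last in-hospital assessment, since Data Analysis speaks of primary data collection ending at Tx and expressly counts receipt after discharge. This is loose wording. On either reading, controls can receive acupressure before the 3-month outcome.

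**Conclusion.** The point holds in a limited form. Followed as written, the exposure odds ratio gives up the randomised comparison and leaves self-selection among controls unadjusted. With no effect of acupressure it would be about 1.2 to 2.7 across the scenarios in which acceptance depends on CIM interest, and 1.0 where it does not. These values rest on assumed rates of CIM use and uptake, full treatment of the NADA arm and complete follow-up; they show a plausible range and do not predict this trial's result. False-positive rates stay below 10% in the simulated scenarios except the strongest (18.2%).

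The documents do not support saying that the result must be biased, or that the flaw reaches the confirmatory analysis. The primary outcome is measured before surgery, and neither it nor the sample size is touched. The supported conclusion is that the one analysis described for 3-month CIM use cannot answer whether the intervention affects CIM decisions.

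**What to change.** - Name the comparison by randomised arm as the main 3-month CIM analysis: intention to treat, logistic regression adjusted for surgery stratum (breast-conserving therapy or mastectomy).
- Word the question as perioperative acupressure versus standard care with acupressure offered at discharge. Report how many controls took up the offer, and state that uptake may dilute the contrast.
- Show the exposure groups descriptively as NADA, accepting controls and declining controls, with a caveat on self-selection and no claim of effect.
- Clarify in the control-group section that the last study measurement means the last in-hospital assessment (Tx), since the 3-month follow-up comes later.

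The cost is wording, plus a narrower and possibly attenuated estimate for one exploratory outcome. Trial conduct and sample size do not change. With 8 of 66 participants recruited at submission, this can be settled well before follow-up data are complete.

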### Ethical Considerations

This study adheres to the principles of the Helsinki Declaration. The study has been approved by the Ethics Committee at the State Medical Association of Baden-Württemberg (Landesärztekammer Baden-Württemberg) (F-2025‐104, 17.11.2025). Written informed consent will be obtained only after adequate explanation has been provided. Participation is voluntary, and patients may withdraw their consent at any time without providing reasons and without any consequences for their medical care. Following informed consent, eligibility will be determined by the study physician or appropriately delegated personnel according to the predefined inclusion and exclusion criteria.

## Results

Funding for the study was confirmed in April 2025. The study is planned for a total duration of 18 months. Based on approximately 200 breast surgeries performed annually at Robert-Bosch-Hospital and an anticipated recruitment rate of 30%, the target sample size of 66 participants is expected to be reached within approximately 12 months. Recruitment began on March 31, 2026. At the time of manuscript submission, 8 participants have been recruited. Recruitment is anticipated to conclude in April 2027, with data collection expected to be completed by July 2027. Study results are projected to be available in September 2027. There was no patient or public involvement in the development of the study design, selection of outcome measures, or planning of the research procedures.

## Discussion

The present trial aims to evaluate the effectiveness of auricular acupressure according to the NADA protocol in addition to standard preoperative care in reducing perioperative anxiety and pain in women with a first diagnosis of breast cancer undergoing therapeutic surgery. It is hypothesized that auricular acupressure will be superior to standard care in reducing perioperative anxiety and pain in this patient population. This hypothesis is in line with previous findings, including both emergency and elective surgeries in clinically heterogeneous populations [15], and initial evidence suggesting beneficial effects of the NADA protocol in oncological patients outside the surgical context [24-26].

This trial has several methodological strengths. To the best of our knowledge, this is the first randomized controlled trial to evaluate NADA auricular acupressure in the perioperative context of breast cancer surgery. By focusing on a standardized 5-point auricular protocol applied within a defined perioperative time frame, this study seeks to address the substantial variability in acupuncture techniques, point selection, and treatment duration from previous research. Furthermore, the use of this standardized protocol enhances reproducibility and may facilitate future implementation in routine clinical care if efficacy is demonstrated. The randomized controlled design with centralized allocation concealment reduces the risk of selection bias. Stratified randomization according to surgical procedure further minimizes potential confounding. Another strength of this trial is that it is conducted within a real-world perioperative oncology setting and embedded into routine clinical care. The intervention is delivered under pragmatic conditions, which enhances the external validity of the findings.

Several limitations must also be considered. Due to the nature of the intervention, blinding of participants and treating personnel is not feasible. This might introduce bias in the measurement of outcomes, particularly in the assessment of patient-reported outcomes such as anxiety and pain. To address this limitation, objective secondary outcomes, including medication use and postoperative complications, are assessed to provide clinically relevant endpoints less susceptible to reporting bias. Furthermore, the study does not include a sham control condition. The primary aim was to evaluate the efficacy of NADA auricular acupressure as an adjunct to routine care rather than to isolate specific acupoint-related effects. Consequently, the design does not allow differentiation between specific physiological effects of point stimulation and nonspecific effects related to expectation, therapeutic attention, or contextual influences. In addition, the sample size estimation was based on detecting a minimal clinically important difference in preoperative state anxiety as measured by the STAI-S. The study is therefore adequately powered for the primary endpoint but is not specifically powered to detect statistically significant differences in secondary outcomes. These should be considered exploratory, and effect estimates and corresponding CIs will be reported to facilitate interpretation of the magnitude and precision of observed differences.

Despite these limitations, the study addresses an important gap in the field of integrative oncology. There is growing interest among patients and health care providers in nonpharmacological strategies to improve perioperative well-being. However, integration of such approaches into clinical practice requires evidence from rigorously designed randomized trials. If NADA auricular acupressure proves effective in reducing perioperative anxiety and pain, it could represent a low-risk, low-cost, and easy-to-implement adjunct to standard care. Conversely, if no significant benefit is observed, the study will still provide important evidence to reconsider current assumptions regarding the role of auricular acupressure in perioperative oncology. Additionally, it will provide valuable information regarding effect sizes and variability in this patient population, thereby informing the planning of following studies.
